**Methods/Design:**

A randomized controlled clinical trial will be conducted. It will involve 60 women ≥ 35 years of age with a diagnosis of FM and TMD. After recruitment, patients will be randomly allocated to one of four groups: a control group (no intervention), a group that will receive a phototherapy intervention (PHO), a group that will be prescribed muscle-stretching, aerobic, and facial exercises (EXT), or a group that will receive phototherapy plus exercise interventions (PHO + EXT). The trial will last 10 weeks, and the following outcomes will be evaluated on two separate occasions (baseline and within 24 h after the last day of the protocol). Pain intensity will be analyzed using a visual analogue scale and the McGill Pain Questionnaire, and pain thresholds will be punctuated using a digital algometer. FM symptoms will be assessed using the Fibromyalgia Impact Questionnaire, and quality of life will be determined with the 36-item Short Form Health Survey. Serotonin levels will be evaluated in salivary samples using a competitive enzyme-linked immunosorbent assay.

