### Population and sample size

In a literature review, we found that FM prevalence is higher in women between ages 35 and 60 years than in men [21]. All women patients aged ≥ 35 years and referred for FM and TMD diagnostic evaluation were eligible for inclusion in the present trial. Patient eligibility comprises an evaluation of medical history, physical examination, and dental and rheumatologic routine evaluations. Moreover, patients had to have undergone FM screening as reported by the American College of Rheumatology using the Fibromyalgia Impact Questionnaire (FIQ) 1. The TMD diagnosis had to be reported on the basis of TMD research diagnostic criteria (axes I and II) [22]. The sample size calculation was based on a previous study by Consalter et al. [23] in which the TMD prevalence was 80 % in patients with FM. A 95 % reliability and a 10 % error rate was assumed to estimate the sample size (n) as follows [24]:$$ n={\left(\frac{z_{a/2}\sqrt{p\left(1-p\right)}}{\varepsilon}\right)}^2={\left(\frac{1.96\ast \sqrt{0.8\ast 0.2}}{0.1}\right)}^2 $$

A total of 60 women will be randomized for this trial, with 20 women allocated per group.

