### Recruitment and inclusion criteria

The recruitment methods include direct referral of patients who consult for FM, in which TMD also will be investigated. A rheumatologist and a dentist will make the diagnoses of FM and TMD, respectively. A physician at each FM medical center will participate. A compatible diagnosis of FM will be obtained on the basis of evaluation criteria similar to those previously well defined [25]. The recruitment of 60 patients is planned to be finished within 24 months. Inclusion criteria are as follows: women ≥ 35 years of age presenting with at least a 5-year diagnosis of FM and TMD, optimized drug treatment, cognitive independence to respond to inquiries, functionally independent regarding daily physical activity, availability and ability to fully comply with the training process and phototherapy, and no contraindication to the research procedures. All centers will be informed about the EXTRAPHOTO trial and its inclusion criteria during department meetings. Exclusion criteria are patients in a prior regular and structured physical activity program; missing more than three times from treatment; presence of psychiatric disorders, missing teeth, and/or use of dentures; a history of trauma to the face; currently undergoing orthodontic intervention; and any contraindication to exercise or phototherapy. The FM symptoms can be confused with other disorders. Thus, women for whom there are suspicions of any of the following disorders will be excluded: osteoarthritis, bursitis, tendinitis, rheumatoid arthritis, palindromic rheumatism, polymyalgic rheumatic disease, hydroxyapatite crystal diseases, systemic lupus erythematous, dermatomyositis-polymyositis complex, Lyme disease, hypothyroidism or hyperthyroidism, hyperparathyroidism, previous history of hepatitis, and history for Epstein-Barr virus infection. Sjögren, McArdle, Addison, Cushing, and paraneoplastic syndromes will also be exclusion criteria.

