### Randomization, blinding, and experimental groups

The EXTRAPHOTO trialists will enroll patients immediately after diagnosis of the two comorbidities and referral from recruitment centers. Patient enrollment and randomization, as well as data management, will be carried out by the Program in Biophotonics Applied to Health Sciences of the Nove de Julho University. The blinding will be applied to patients receiving phototherapy and a researcher reported to guide the exercise training. Thus, a researcher will be responsible for programming the phototherapy device, which can be turned on (phototherapy) or off (placebo) prior to application based on the randomization. A second researcher will guide the exercise training and will be blinded for phototherapy and/or placebo procedures. A third investigator will be blinded to allocation and will independently assess the outcomes. The statistical analysis will be performed by a fourth researcher, who will also be blinded to allocation of the patients.

The eligible participants will be instructed not to change their lifestyle or pharmacologic therapy during the study and will be randomized to one of the following groups:Control (CON): patients not subjected to any intervention; the phototherapy device will be turned off (placebo) as a blinded procedure for these participantsPhototherapy (PHO): patients subjected to phototherapyExercise training (EXT): patients subjected to aerobic exercise; the phototherapy device will be turned off (placebo) as a blinded procedure for these participantsPhototherapy plus exercise training (PHO + EXT): patients subjected to phototherapy and aerobic exercise training

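### The protocol states 60 women and 20 per group, but it has four randomised groups: four groups of 20 need 80 women, and 60 women give 15 per group.

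*Protocol article*

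**What the plan says.** The sample size statement in the protocol article (Population and sample size) is: "A total of 60 women will be randomized for this trial, with 20 women allocated per group".

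The total of 60 appears in two other places. The Abstract says "It will involve 60 women", and Recruitment and inclusion criteria says "The recruitment of 60 patients is planned to be finished within 24 months". The figure of 20 per group appears only in the sample size section.

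The Abstract gives the number of groups: "patients will be randomly allocated to one of four groups". The section Randomization, blinding, and experimental groups says that eligible participants "will be randomized to one of the following groups" and lists CON, PHO, EXT and PHO + EXT. The legend of Fig. 1 names the same four.

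The total is derived from a precision formula for one proportion. Its inputs are that "the TMD prevalence was 80 % in patients with FM" and that "A 95 % reliability and a 10 % error rate was assumed to estimate the sample size".

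**The concern.** The total, the group size and the number of groups are tied by multiplication, and the three stated values do not fit together. A reader cannot tell whether full enrolment means 60 women or 80.

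The group size fixes the make-up of the allocation list and the information in every between-group comparison. Trial status says that women are already being allocated, so a list built on one of the two figures is presumably in use. If the sentence stays as it is, the final report will depart from the protocol whichever figure was followed: it will show either a shortfall per group or an overrun of the total and of the recruitment target.

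**Working it through.** **Inputs from the article.** Total randomised 60; women per group 20; randomised groups 4; p = 0.80; z = 1.96; margin 0.10; two-sided significance level 0.05 (Statistical analysis).

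**Step 1: the article's own total.** n = (1.96 × √(0.8 × 0.2) / 0.1)² = 61.47, which rounds up to 62. The stated 60 is within 2 women of this, so the total roughly reproduces. The formula has no term for the number of groups, so it cannot yield a group size.

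**Step 2: the group size.**
- 4 × 20 = 80, not 60. The excess is 20 women, and 20/60 is one third.
- 60 / 4 = 15, not 20. The shortfall is 5 per group, and 5/20 = 25%.
- 60 / 3 = 20. Only a three-group design fits both figures, and the article describes none.

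**Step 3: the one precision the article does use.** The half-width for the prevalence is 1.96 × √(0.16/n): 10.1 percentage points at n = 60 and 8.8 at n = 80. It depends on the total only.

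**Step 4: illustration of what 15 or 20 per group means.** The article gives no target difference, SD, power or number of comparisons. The values here are therefore assumptions: differences of 0.5, 0.8 and 1.0 SD, and six pairwise comparisons among four groups for the Bonferroni case. The model is a plain comparison of two group means after treatment, with the variance pooled over four groups. Degrees of freedom are 4n − 4, which is 56 at n = 15 and 76 at n = 20. The non-centrality is d × √(n/2), and power is the chance that the non-central t exceeds the critical value.

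| | 15 per group | 20 per group |
|---|---|---|
| Critical t, two-sided 0.05 | 2.003 | 1.992 |
| Detectable difference, 80% power | 1.04 SD | 0.90 SD |
| Power at 0.5 / 0.8 / 1.0 SD, level 0.05 | 27% / 58% / 77% | 35% / 70% / 88% |
| Power at 0.5 / 0.8 / 1.0 SD, level 0.05/6 | 10% / 30% / 51% | 14% / 43% / 67% |

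For example, at n = 15 and d = 0.8 the non-centrality is 0.8 × √7.5 = 2.19, and power is about 58%. At n = 20 it is 0.8 × √10 = 2.53, and power is about 70%.

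**The case against.** **It may be a slip in one sentence.** The total of 60 appears three times and sits near the formula result, while 20 per group appears once. If the list is already 15 per group, nothing in the conduct of the trial changes. This stands as the likelier explanation, but the article does not settle it. Fig. 1 is not visible in the text available here. It might show which figure was meant, but it could not make four groups of 20 equal 60.

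**Could the design escape the contradiction?** Unequal allocation would not help, because 20 is given as the size of each group. Leaving the control group out of the count would not help either, because it is listed among the randomised groups and the 60 are those randomised.

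**A reader might infer that the plan's stated precision or power is wrong.** The article does not support that. It makes no between-group precision or power statement, and its one precision input, the 10% margin on prevalence, does not depend on group size.

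**The illustration has limits.** It rests on assumed differences and an assumed six pairs. The planned repeated-measures analysis uses a baseline, so its precision also depends on a baseline correlation that the article does not give. The figures show direction and rough size only.

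**Conclusion.** The contradiction is certain and rests on the article's own figures. With four randomised groups, either the group size is 15 (25% below the stated 20) or the total is 80 (a third above the stated 60). The balance of the text favours 60 women with 15 per group, but only the allocation list can confirm it.

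Under the assumptions stated above, the choice moves the difference detectable with 80% power between about 1.04 and 0.90 SD, and moves power for a 0.8 SD difference by about 12 to 13 percentage points.

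Two further readings go beyond the article. One is that the trial will end 20 women short of its plan: this is not shown, because the list may have been built for 60 from the start. The other is that correcting the sentence makes the sample size sound: it does not, because a formula for estimating a prevalence justifies neither 15 nor 20 per group for comparing pain. That is a separate matter and would remain.

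**What to change.** 1. Check the allocation list in use, and the arm sizes in Fig. 1 if it gives them.
2. If the list is for 60, change the sentence under Population and sample size to 60 women, 15 per group. This is the default.
3. If the list was built for 80, keep 20 per group and correct the total to 80 in the Abstract, in Population and sample size, and in Recruitment and inclusion criteria. Review the 24-month recruitment target against the new total.
4. State which figure the list followed and that the other was an error. Do not present the correction as a justification of the sample size for the pain comparison.

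The cost of the default is one check and one corrected sentence, with no extra patients, though the stated group size becomes smaller. The alternative needs three corrections and 20 more women than the stated 60.

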### Recruitment and inclusion criteria

The recruitment methods include direct referral of patients who consult for FM, in which TMD also will be investigated. A rheumatologist and a dentist will make the diagnoses of FM and TMD, respectively. A physician at each FM medical center will participate. A compatible diagnosis of FM will be obtained on the basis of evaluation criteria similar to those previously well defined [25]. The recruitment of 60 patients is planned to be finished within 24 months. Inclusion criteria are as follows: women ≥ 35 years of age presenting with at least a 5-year diagnosis of FM and TMD, optimized drug treatment, cognitive independence to respond to inquiries, functionally independent regarding daily physical activity, availability and ability to fully comply with the training process and phototherapy, and no contraindication to the research procedures. All centers will be informed about the EXTRAPHOTO trial and its inclusion criteria during department meetings. Exclusion criteria are patients in a prior regular and structured physical activity program; missing more than three times from treatment; presence of psychiatric disorders, missing teeth, and/or use of dentures; a history of trauma to the face; currently undergoing orthodontic intervention; and any contraindication to exercise or phototherapy. The FM symptoms can be confused with other disorders. Thus, women for whom there are suspicions of any of the following disorders will be excluded: osteoarthritis, bursitis, tendinitis, rheumatoid arthritis, palindromic rheumatism, polymyalgic rheumatic disease, hydroxyapatite crystal diseases, systemic lupus erythematous, dermatomyositis-polymyositis complex, Lyme disease, hypothyroidism or hyperthyroidism, hyperparathyroidism, previous history of hepatitis, and history for Epstein-Barr virus infection. Sjögren, McArdle, Addison, Cushing, and paraneoplastic syndromes will also be exclusion criteria.

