### Interventions

The trial will be 10 weeks long, during which time patients will undergo two sets of phototherapy, exercise, or placebo procedures per week. Phototherapy will be applied 30 min before each exercise bout, and treatment sessions will be carried out Tuesdays and Thursdays each week. For eligible patients, the research will record outcome parameters at baseline prior randomization and 48 h after the last day of intervention. This evaluator will be blinded to the allocation of the patients into the respective groups.

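### An attendance rule that can only apply after randomisation is listed as an exclusion criterion, so on its ordinary reading randomised women are removed for missing sessions

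*Protocol article*

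**What the plan says.** In the protocol article, Recruitment and inclusion criteria, the exclusion list opens with "Exclusion criteria are patients in a prior regular and structured physical activity program". The next item is "missing more than three times from treatment". Baseline conditions follow, such as psychiatric disorders, dentures, facial trauma and current orthodontic work. The same section already has a separate inclusion criterion on expected compliance: "availability and ability to fully comply with the training process and phototherapy".

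Interventions sets the schedule: "The trial will be 10 weeks long, during which time patients will undergo two sets of phototherapy, exercise, or placebo procedures per week". It also fixes the order of events: "the research will record outcome parameters at baseline prior randomization and 48 h after the last day of intervention". Under Randomization, blinding, and experimental groups, eligible women are randomised to one of four groups, and treatment comes after that.

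Statistical analysis names the tests (repeated-measures ANOVA, or Kruskal-Wallis) but no analysis population. No section says what happens to the final assessment or the data of a woman who meets the attendance rule.

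**The concern.** An exclusion criterion should be decidable before allocation. This one depends on how a woman behaves under the treatment she was allocated. If it is applied as listed, the women left in each arm are no longer the women randomised to it.

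The rule could act unequally. EXT and PHO + EXT add 30 minutes on a treadmill, a stretching programme and facial exercises to the device session. In women with chronic pain and fatigue, missing sessions may be related to pain, which is the primary endpoint. If more women are removed from one arm, and those removed would have scored differently from those kept, the comparison shifts without any treatment effect. Blinding the assessor and the analyst does not repair this, because the selection occurs before either sees the data.

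**Working it through.** **Can the rule act before randomisation?** Baseline is recorded before randomisation and the trial sessions come after it. The earliest a woman can meet the rule is her fourth missed session. It is unlikely to mean expected attendance, because that is already an inclusion criterion.

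**Threshold.** 10 weeks × 2 sessions = 20 sessions. More than three missed means four or more missed, so 16 or fewer attended. Staying in requires at least 17 of 20, which is 85%.

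**Arm size.** Population and sample size states "A total of 60 women will be randomized for this trial, with 20 women allocated per group", but four groups of 20 would be 80. Sixty women in four equal groups gives 60 / 4 = 15, used below. That mismatch is a separate matter.

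**How many women the rule could remove.** The documents give no rate of missed sessions. Assume each session is missed independently with probability m. The share removed is then P(X ≥ 4), with X binomial (20, m).

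| Assumed m | Share removed | Of 60 | Of 15 |
|---|---|---|---|
| 5% | 1.6% | 1.0 | 0.2 |
| 10% | 13.3% | 8.0 | 2.0 |
| 15% | 35.2% | 21.1 | 5.3 |
| 20% | 58.9% | 35.3 | 8.8 |

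**Illustrative bias with no true effect.** Suppose a normal attendance propensity correlates ρ with outcome, and the lowest fraction q of an arm is removed. The mean outcome of those retained shifts by ρ × φ(c) / (1 − q) SD, where c = Φ⁻¹(q). The factor φ(c) / (1 − q) is 0.195 at q = 10% and 0.350 at q = 20%. The bias is the difference in shift between two arms. With ρ assumed to be 0.3 to 0.5:

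- 20% versus 10% removed: (0.350 − 0.195) × 0.3 to 0.5 = 0.05 to 0.08 SD.
- 20% versus none removed: 0.350 × 0.3 to 0.5 = 0.10 to 0.17 SD.
- Equal removal with equal ρ: 0.
- Equal removal of 20%, but ρ = 0.5 in one arm and 0.3 in the other: 0.350 × 0.2 = 0.07 SD. Equal counts alone are therefore not enough to rule bias out.

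Feeding the binomial shares into the same formula, miss rates of 10% versus 15% give 0.10 SD at ρ = 0.3 and 0.16 SD at ρ = 0.5. Miss rates of 10% versus 20% give 0.21 and 0.35 SD.

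**Precision.** With 15 per arm, the difference detectable at two-sided 5% and an assumed 80% power, before any Bonferroni adjustment, is about 1.06 SD. Losing 3 of 15 raises it to about 1.06 × √(15/12) = 1.19 SD.

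**The case against.** The strongest objection is that the consequence is inferred. The article does not say whether an excluded woman stops treatment, is not assessed, or is dropped from analysis, and the full protocol and analysis plan are not shown. This stands in part. A reader might conclude that the plan prescribes a completers-only analysis, but the text does not say so. Removal from the trial is only the ordinary meaning of an exclusion criterion. Nothing shown contradicts that meaning, and the rule is stated in the article itself, so this is not a detail left to another document.

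A reader might also infer that exclusions will be concentrated in the exercise arms and will favour them. The documents do not support that:

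- They contain no attendance data. Control women receiving only a sham may miss visits because they notice no benefit, which could reduce or reverse the difference.
- The burden common to all arms is not small. Each point takes 300 s. If the roughly nine listed tender sites were each treated once, plus both jaw joints, a session would last 11 × 300 s = 55 minutes. This is an assumption, since only painful points are treated. CON and EXT receive the sham version.
- PHO + EXT versus EXT and PHO versus CON have matched visit burden, so a burden-driven difference bears mainly on exercise versus no-exercise contrasts.

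Finally, deleting the criterion is not sufficient. Some poor attenders will not return, and an ANOVA on two time points normally needs both values. That stands, and the fix covers it.

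**Conclusion.** The point holds. As written, a post-randomisation attendance rule sits among the eligibility criteria, and on its ordinary reading it removes randomised women, with no statement that they are still assessed or analysed.

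The potential bias falls mainly on contrasts between exercise and no-exercise arms. Its sign depends on which arm loses more women and on whether poor attenders fare worse or better; the documents settle neither. The SD figures rest entirely on assumed exclusion rates and correlations. In the moderate case (20% versus 10% removed) they are small beside the difference that 15 per arm could detect. The loss of sample does not depend on any imbalance: if session absence averaged 10%, about 8 of 60 women would be removed, again an assumed rate.

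**What to change.** Take the item out of the exclusion criteria. Record attendance as adherence and report it by group. Invite every randomised woman to the existing post-treatment assessment, whatever her attendance. Analyse all women with outcome data in their allocated group, and state a method for missing final values. Keep attendance at 17 or more of the 20 sessions only as the definition of a per-protocol sensitivity analysis. This concerns assessment and analysis only; whether a poor attender continues treatment is a clinical matter on which no change is proposed.

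The cost is one deleted criterion, a short statement on analysis and missing values, and some follow-up effort for poor attenders. The main estimate will be slightly diluted relative to full attenders, which the sensitivity analysis will still show. Trial status reports that allocation is still under way, so the change can be made before analysis. If any women have already been excluded under the rule, report their number by group and seek their final assessment where that is still possible.

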### Randomization, blinding, and experimental groups

The EXTRAPHOTO trialists will enroll patients immediately after diagnosis of the two comorbidities and referral from recruitment centers. Patient enrollment and randomization, as well as data management, will be carried out by the Program in Biophotonics Applied to Health Sciences of the Nove de Julho University. The blinding will be applied to patients receiving phototherapy and a researcher reported to guide the exercise training. Thus, a researcher will be responsible for programming the phototherapy device, which can be turned on (phototherapy) or off (placebo) prior to application based on the randomization. A second researcher will guide the exercise training and will be blinded for phototherapy and/or placebo procedures. A third investigator will be blinded to allocation and will independently assess the outcomes. The statistical analysis will be performed by a fourth researcher, who will also be blinded to allocation of the patients.

The eligible participants will be instructed not to change their lifestyle or pharmacologic therapy during the study and will be randomized to one of the following groups:Control (CON): patients not subjected to any intervention; the phototherapy device will be turned off (placebo) as a blinded procedure for these participantsPhototherapy (PHO): patients subjected to phototherapyExercise training (EXT): patients subjected to aerobic exercise; the phototherapy device will be turned off (placebo) as a blinded procedure for these participantsPhototherapy plus exercise training (PHO + EXT): patients subjected to phototherapy and aerobic exercise training

